### Potential benefits of TaTME rectal resections

TaTME offers better access to the lower rectum in a difficult pelvis and also facilitate a clear distal margin by insertion of a distal to the tumour purse string under direct vision. This enables an end-to-end anastomosis without the need of multiple stapler firings. This approach also allows two-team synergy with an abdominal and perineal surgeon operating simultaneously.

The technique however still requires significant surgical skills and the ability to operate in a confined space.

The objective of this study is to compare TaTME and RLAR in expert hands. Outcome measures are mainly focused on differences in oncological long-term effects, see ***Table 1*** for details.

**Table 1 T1:** Trial specific primary and secondary outcome measures.

OBJECTIVES	OUTCOME MEASURES	TIME POINT(S) OF EVALUATION OF THIS OUTCOME MEASURE (IF APPLICABLE)

**Primary Objective** 3 year disease free survival after RLAR and TaTME	3 year disease free survival	6 monthly post op for the first 2 years and 12-monthly follow-up for next 3 years

**Secondary/exploratory Objectives** Surgical morbidity/mortality up to 90 days		90 days

Pathological quality assessment	Pathological assessment of mesorectum: Distal resected margin ≥1 cm Lymph node yield Mesorectal plane of surgery R0 resection (all margins clear)	

Assessment of intraoperative adverse events	To report “near misses” and associated impact upon clinical outcomes	

Overall survival at 3 years		

Health economics assessments	Healthcare resource utilization (costs) including hospital length of stay, ICU hours, and productivity losses collected through a Labour Force survey). Return to work/activity will also be included	

Evaluation of the operative length of time	Total OR utilisation time and operative time skin to skin, minutes	

Recruitment per month per centre for the RLAR and TaTME arms	Patients dropout rate during follow-up will also be monitored	

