### The Number of Participants

The primary study end point, DFS is defined as the time following successful surgery to the first date of local, regional/distant relapse or death due to colorectal cancer (patients with secondary malignancy will be censored). Overall survival is defined as the time following successful surgery to death.

In the TaTME, it is assumed that the DFS is 92% and in the RLAR arm 95% at 3 years. A non-inferiority margin of 90% is selected. Based on this estimation, sample size calculation has been done with a one-sided level of significance of 20% and a power of 80%. A total number of 330 patients is needed, 165 patients in the RLAR arm and 165 patients in the TaTME are required with a 10% loss to follow-up assumed.

DFS will be analysed on an intent-to-treat (per protocol) basis using a log-rank test after propensity matching analysis has been conducted; a secondary analysis of DFS will also performed be using a Cox proportional hazards regression model with the unmatched cohort (without adjustment of baseline characteristics, i.e. propensity score match) that allowed for the effect of treatment and include lists of covariate with a statistical interaction of alpha level of 20%.

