## Discussion

To date studies on TaTME and robotic TME have focused mainly on short term outcomes and oncological endpoints such as specimen quality, circumferential resection margin involvement and the free distal margin [13,16,17].

In a recent study comparing TaTME and Robotic TME, there were no differences in the incidence of poor quality. However the authors noted that distal resection margin (DRM) involvement was higher in the TaTME group [16]. They attributed this to the learning curve effect of TaTME. As discussed earlier, previous reports have noted that the learning curve for robotic TME was less than laparoscopic surgery, which in effect TaTME is still a laparoscopic “bottom up” approach.

Nonetheless, the long-term oncological parameters for both procedures, including overall survival, disease-free survival and local recurrence, are yet to be clarified. Secondly, there have been significant concerns in regards to an increased recurrence rate after TaTME [18]. The Norwegian group have noted an unexpected increase in local recurrence after TaTME of 9.5% after a median of 11 months after surgery [18]. The reasons for their observations is unclear, despite that fact that their surgeons performing TaTME were experienced and were proctored and trained in England and Spain for the procedure.

In 1980 Knight and Griffen [19] publised their stapling technique for low rectal cancer anastomosis using linear and circular stapler. This has led to the introduction of the double stapling technique [20]. The advantage is that the distal segment of the bowel is not opened and this avoids spillage from the rectal stump.

The possibility of increased local recurrences in TaTME may be related to the rectal transection and air flow during dissection from the perineum. The rectal purse-string suture is never completely air tight and this will invariably lead to shredding of microscopic cancer cells in the pelvis and hence this may lead to an increase rate of local recurrence. During a robotic TME and the use of the articulating robotic stapler, the rectal transection is precise and there are no leakage of microscopic cancer cells in the pelvis.

With these current issues in mind, we aim to compare the 3 year disease free survival and local recurrence rate of the two procedures performed by experienced surgeons who are beyond their learning curve. Only surgeons who have performed more than 60 procedures in either TaTME or robotic TME will be selected.

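### The 90% non-inferiority margin has no scale, test arm or reference arm, so the stated 80% power cannot be tied to a stated hypothesis

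*Protocol article*

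**What the plan says.** All design figures are in the protocol article under The Number of Participants.

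- Planning values: "In the TaTME, it is assumed that the DFS is 92% and in the RLAR arm 95% at 3 years".
- Threshold: "A non-inferiority margin of 90% is selected".
- Error rates: a "one-sided level of significance of 20" per cent, with 80% power.
- Size: "A total number of 330 patients is needed, 165 patients in the RLAR arm and 165 patients in the TaTME are required". Attrition of 10% is allowed for.
- Primary analysis: a log-rank test after propensity matching. No confidence limit or non-inferiority test is described.

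The section on the potential benefits of TaTME puts the aim as a plain comparison: "The objective of this study is to compare TaTME and RLAR in expert hands". Table 1 lists 3-year DFS as the primary outcome. Neither place says which technique must be shown to be no worse than the other.

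**The concern.** A non-inferiority margin is the largest loss that would be tolerated in a named test arm relative to a named reference, on a named scale. A bare 90% supplies none of these. It could mean that 3-year DFS must not fall below 90%, that a loss of 10 points is acceptable, or that the DFS ratio must exceed 0.90. Each can be read with either technique as the test arm.

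Two things are at stake. First, the conclusion: the same data can pass under one reading and fail under another, so the choice could be made after the results are known. Second, the power claim: 80% is a property of a specific hypothesis, and none is written down.

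**Working it through.** **Inputs, all from The Number of Participants:** DFS 0.92 (TaTME) and 0.95 (RLAR), one-sided alpha 0.20, power 0.80, 165 enrolled per arm, 10% loss. Evaluable per arm: 165 × 0.9 = 148.5.

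**Binary 3-year DFS, difference scale**

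n per arm = (z₀.₈₀ + z₀.₈₀)² × [0.92 × 0.08 + 0.95 × 0.05] / d², where d is the margin plus the assumed true advantage of the test arm.

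(0.8416 + 0.8416)² = 2.833. The variance term is 0.0736 + 0.0475 = 0.1211. So n = 0.3431 / d².

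Power at 148.5 per arm = Φ(d/SE − 0.8416), with SE = √(0.1211/148.5) = 0.0286.

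**Ratio 0.90, log scale**

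The variance term is 0.08/0.92 + 0.05/0.95 = 0.1396. The distance is ln(0.92/0.95/0.90) = 0.0733 with TaTME tested, and ln(0.95/0.92/0.90) = 0.1374 with RLAR tested.

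| Reading of 90% | d | Evaluable per arm | Enrolled per arm (÷ 0.9) | Power at 148.5 |
|---|---|---|---|---|
| DFS floor, RLAR vs TaTME (2-point margin) | 0.02 + 0.03 = 0.05 | 138 | 154 | 82% |
| DFS floor, TaTME vs RLAR (5-point margin) | 0.05 − 0.03 = 0.02 | 858 | 954 | 44% |
| 10-point loss, TaTME vs RLAR | 0.10 − 0.03 = 0.07 | 71 | 79 | 95% |
| 10-point loss, RLAR vs TaTME | 0.10 + 0.03 = 0.13 | 21 | 24 | over 99% |
| Ratio 0.90, TaTME/RLAR | 0.0733 (log) | 74 | 83 | 94% |
| Ratio 0.90, RLAR/TaTME | 0.1374 (log) | 21 | 24 | over 99% |

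The plan's figure is 165 enrolled. The first row is nearest. A Farrington-Manning calculation moves it to 141 evaluable, 157 enrolled.

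**The nearest reading as a log-rank test**

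Under proportional hazards, the floor is a hazard ratio of ln 0.90 / ln 0.92 = 1.264. The assumed hazard ratio is ln 0.95 / ln 0.92 = 0.615. The log distance is ln(1.264/0.615) = 0.720.

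Events = 4 × 2.833 / 0.720² = 21.9.

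- Exactly 3 years of follow-up: the mean event probability is (0.08 + 0.05)/2 = 0.065, so 21.9 / (2 × 0.065) ≈ 168 per arm before loss. Power is 77% at 148.5 and 79.5% at 165 with loss ignored.
- Mean follow-up of 3.4 years (an assumption, not stated in the article): event probabilities are 1 − 0.92^(3.4/3) = 0.090 and 1 − 0.95^(3.4/3) = 0.056, with mean 0.0733. This gives 149 evaluable, 166 enrolled and 80% power at 148.5.
- Over assumed mean follow-up of 3.0 to 4.0 years, the enrolled number runs from 187 to 142 per arm.

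**What the nearest reading depends on**

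Keep the 2-point margin and set both arms to 92%. SE = √(2 × 0.0736/148.5) = 0.0315, and power = Φ(0.02/0.0315 − 0.8416) = 42%. With TaTME as the test arm and the same 90% floor, power is 44% (37% as a log-rank test at 3 years).

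**One data set, different conclusions**

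Suppose 92% and 95% are observed in 148.5 per arm. The one-sided 80% limit lies 0.8416 × 2.86 = 2.4 points from the estimate. For TaTME minus RLAR the lower limit is −3 − 2.4 = −5.4 points, which fails a 5-point margin and passes a 10-point one. For RLAR minus TaTME it is 3 − 2.4 = +0.6 points, which passes any margin.

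**The case against.** The strongest reply is that this is poor wording rather than failed arithmetic. A reader might infer from the table that no interpretation yields 165 per arm at 80% power. The figures do not support that. Testing RLAR against TaTME with a 90% floor gives about 82% power at the stated size after loss. Its log-rank form, the test the article names, gives 166 enrolled per arm if mean follow-up is 3.4 years. Table 1 schedules visits over 5 years, so follow-up beyond 3 years is plausible. This stands: the sample size may well come from such a calculation. But nothing in the article says so, and the match needs a direction and a follow-up time that are not stated.

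A reader might also infer that the Discussion refutes the 92% input, because it reports an "unexpected increase in local recurrence after TaTME of 9.5% after a median of 11 months after surgery", which already exceeds the 8% of events assumed over 3 years. That does not follow. It is one external group's result. The article calls its cause unclear and gives no caseload for those surgeons, whereas this trial sets a 60-procedure experience threshold. It shows that 92% may be optimistic and justifies a sensitivity range, not a contradiction. Such a range must hold the rule fixed. At DFS of 90%/93% or 85%/88%, power is 76% or 66% for a fixed 2-point difference, but a 90% floor would then be a margin of zero or lie above the reference.

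Finally, the article condenses a fuller protocol, which may show the calculation. That would excuse an omission. Here the article prints a margin that is not usable as worded.

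**Conclusion.** The point holds in a limited form. The 90% figure cannot serve as a margin as written, and the planned log-rank test gives no other criterion by which non-inferiority would be judged. Across the binary readings, the same stated inputs imply between 24 and 954 enrolled per arm, and power at the stated size runs from 44% to over 99%. One unstated reading fits approximately (77% to 82% power, depending on method and follow-up), and its fit rests on RLAR being truly 3 points better. The 80% power is therefore neither verified nor disproved. It simply belongs to no hypothesis that the article states.

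Assumptions: binary 3-year DFS or proportional hazards, with patients lost to follow-up contributing no information. Patients dropped in propensity matching are ignored and would lower every power figure further.

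**What to change.** Replace the margin sentence with an explicit decision rule that names:

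- the test arm and the reference arm;
- the margin, either as an absolute difference in 3-year DFS or as a hazard ratio;
- the one-sided confidence level (80% if the 20% alpha is kept).

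The sponsor chooses the margin and direction. State that the primary analysis after matching reports the confidence limit on that same scale and compares it with the margin, instead of only a log-rank p-value.

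Keep 330 patients and restate the power for that rule under the planning values, under equal DFS in both arms, over a range of lower DFS values, and allowing for patients lost to matching. Show the formula and the follow-up time assumed.

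The cost is one paragraph of text and a recalculation, with no added patients. The restated power may be less favourable than 80%.

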#### Operator Learning Benefits

The main criticisms of robotic TME are the longer operating times and higher costs, compared to laparoscopic TME [13]. More widespread use of and familiarity with the robotic system has led to significant improvements in operation time, rates of conversion to open surgery and the number of harvested lymph nodes.

Bokhari et al. [14] suggested that the learning curve of robotic colorectal surgery was passed at 15 to 25. Kim et al. showed that the learning curve plateaued after 65 cases for Laparoscopic TME as opposed to 32 cases for Robotic TME [15].

Most studies to date about RLAR were done using the da Vinci Si system or older models. With the newer systems X or Xi, and once the surgeons have achieved at least 60 procedures we believe that the outcomes and operating time is less, that has been recently published by the ROLAR trial [11]. Similarly; to achieve good clinical and oncological outcomes with TaTME, surgeons are required to have performed at least 60 cases. Hence we decided to choose 60 procedures as an arbitrary number to select our surgeons experience involved in this trial.

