## Methods/design

### Design

This is an observational prospective, multicentre trial. Patients will be assigned either RLAR or TaTME depends on the chosen centres. The centres do either TaTME or RLAR for rectal cancer management according to their training and experience. The study will include 330 patients from a number of international sites. This study has no impact on staging investigations, timing of surgery or any other aspect of the patients’ pre, peri or post-operative care. All decisions remain with the local clinician multi-disciplinary team including when to discharge from hospital. However, the biostatisticians performing the analysis will be blinded to the intervention. For study flow see ***Figure 1***.

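### The primary disease-free survival analysis carries two inconsistent population labels, intention-to-treat and per-protocol, and the protocol does not say which one governs

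*Protocol article*

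**What the plan says.** The only statement of the primary analysis population is in the Protocol article, The Number of Participants: "DFS will be analysed on an intent-to-treat (per protocol) basis", by a log-rank test carried out after propensity matching. The same section sets a non-inferiority margin and defines the endpoint: "DFS is defined as the time following successful surgery to the first date of local, regional/distant relapse or death due to colorectal cancer".

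The Design section adds "This is an observational prospective, multicentre trial" and "Patients will be assigned either RLAR or TaTME depends on the chosen centres". It also says that "the biostatisticians performing the analysis will be blinded to the intervention".

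Conversion appears once, as background in Operator Learning Benefits, where "rates of conversion to open surgery" are listed among the things that improved with familiarity with the robot. The article gives no conversion rate for this study and no rule for classifying a converted case.

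**The concern.** Intention-to-treat and per-protocol are the standard names of two sets that overlap largely but follow different rules. Under the first, a patient whose operation was converted or abandoned stays in the planned group. Under the second, such a patient is usually dropped. Placing one in brackets after the other treats them as synonyms, so the primary comparison has no unique definition.

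Three features of this study make that matter:

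- The comparison is framed as non-inferiority, where exclusions after treatment can change the answer.
- There is no randomisation. Technique follows the centre, so intention has to be defined, as either the centre's technique or the procedure planned for the patient. The article does not say which.
- The Background recommends both techniques for obesity, a narrow male pelvis and bulky low tumours. Those are plausibly the cases most likely to be converted, and removing them would be selection on something that happens after treatment starts.

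**Working it through.** **Does any other text settle the label?**

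- Design: assignment by centre identifies the technique a centre uses, but does not say whether a patient whose procedure changed is kept.
- Endpoint definition: the clock starts at surgery that was successful. That is a condition met or failed after treatment begins, and it points towards a restricted set, against the intention-to-treat label. The Abstract defines successful outcomes by a clear circumferential margin and no Clavien-Dindo grade III–IV complication within 30 days, but the article does not say whether that meaning applies to the DFS clock.
- Propensity matching: the log-rank test is run after matching, so the choice of set also decides which patients can be matched.

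None of these names the primary set.

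**How sensitive is the estimate?** The plan gives no figure for this point, so there is none to reproduce. Inputs from The Number of Participants are 165 patients per arm, 10% loss to follow-up, and "In the TaTME, it is assumed that the DFS is 92% and in the RLAR arm 95% at 3 years". The 165 is taken as given. It could not be reproduced from the stated inputs, but that is a separate matter and this point does not depend on it.

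- Evaluable per arm, before matching: 165 × 0.90 = 148.5
- Expected RLAR events: 148.5 × (1 − 0.95) = 7.4
- Expected TaTME events: 148.5 × (1 − 0.92) = 11.9
- Total: 7.4 + 11.9 = 19.3
- Weight of one event: 100 / 148.5 = 0.67 percentage points

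**Illustration of an exclusion.** Assume that 2% to 10% of an arm is converted: 148.5 × 0.02 = 3.0 and 148.5 × 0.10 = 14.9, or about 3 to 15 patients. Assume also that 3 TaTME events fall among them. Excluding a patient removes both the event and the denominator:

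| TaTME patients excluded | Events excluded | Events / patients left | 3-year DFS |
|---|---|---|---|
| 0 | 0 | 11.88 / 148.5 | 92.0% |
| 3 | 3 | 8.88 / 145.5 | 93.9% |
| 15 | 3 | 8.88 / 133.5 | 93.3% |
| 15 | 1.2 (planned 8%) | 10.68 / 133.5 | 92.0% |

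The shift is upward, by 1.3 to 1.9 points, against an assumed difference between arms of 95 − 92 = 3 points. Three events among 3 to 15 patients is an event rate of 20% to 100%, far above the planned 8%. In the last row the excluded patients have the planned rate and the estimate does not move. The size of the effect therefore depends on how much worse the excluded patients do, and on whether exclusions differ between arms.

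**The case against.** Several counter-arguments have weight.

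- **The bracket may be loose wording** for what the protocol prescribes. That is possible. But next to intention-to-treat, in a plan with a non-inferiority margin, it reads as the name of the other set. If the loose meaning was intended, deleting the bracket costs nothing.
- **The sets may differ little.** Each centre performs one technique, so crossover between the two is unlikely by design, and the article does not make conversion a protocol deviation. This stands, and it limits the expected size.
- **Definitions of analysis sets usually sit in the SAP, which is not shown, and this article is condensed.** That excuses missing detail. Here a rule is stated, for the primary endpoint, in contradictory terms, and a SAP adopting either set would agree with it.

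A reader might infer that the population can be picked once conversions are known. The article does not show that: the analysts are blinded to the intervention, and the unseen SAP may fix the set in advance. A reader might also infer that excluding converted patients could carry TaTME from 92% down to 90%. The arithmetic rules this out for patients who have events, because removing them raises DFS. In addition, reading the 90% margin as a DFS floor is an interpretation, since its scale is not stated.

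**Conclusion.** The contradiction is in the current text and is not resolved elsewhere in the article. The primary DFS analysis names two mutually inconsistent sets, and either would comply. They are different sets, not opposite ones, since most patients would belong to both.

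Only the sensitivity can be sized. With about 19 expected events, each is worth about 0.7 points in its arm, so the status of a few patients can be visible in the result. The illustrated rise from 92% to between 93.9% and 93.3% rests on an assumed 2% to 10% conversion rate and an assumed 3 events among those patients, in one arm only. It is not a forecast, and the effect shrinks to nothing as the event rate of excluded patients approaches the planned one. The finding rests on the wording and needs none of these assumptions.

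**What to change.** In The Number of Participants:

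1. Delete the per-protocol bracket. State that the primary analysis classifies all enrolled patients by the technique planned at enrolment, regardless of conversion.
2. State that this set is fixed before propensity matching, and that the log-rank test is run on the matched patients drawn from it. All enrolled patients then enter the matching, although some may remain unmatched.
3. Run DFS from the date of surgery instead of from surgery judged successful, so that the time origin does not exclude patients on a post-treatment condition.
4. Name per-protocol, defined as planned technique completed, as a supportive analysis.

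A rule that non-inferiority is claimed only if both analyses agree is not needed to remove the contradiction.

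The cost is a sentence or two and one extra analysis. The planned technique has to be recorded at enrolment if it is not already.

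### The trial is sized for non-inferiority in 3-year DFS, but the named primary log-rank test uses no margin, and the stated 80% power does not carry over to it

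*Protocol article*

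**What the plan says.** All the design statements are in the protocol article under Methods/design, The Number of Participants.

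- Assumed rates: "In the TaTME, it is assumed that the DFS is 92% and in the RLAR arm 95% at 3 years".
- Margin: "A non-inferiority margin of 90% is selected". The sentence gives no scale, reference arm or direction.
- Error rates: one-sided alpha 20%, power 80%.
- Size: "A total number of 330 patients is needed, 165 patients in the RLAR arm and 165 patients in the TaTME are required". This total allows for one patient in ten being lost.
- Primary analysis: DFS is compared "using a log-rank test after propensity matching analysis has been conducted". No margin, shifted null hypothesis or confidence limit is attached to the test.
- Secondary analysis: a Cox model in the unmatched cohort, also not tied to the margin.

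Table 1 names 3-year DFS as the primary outcome measure and gives its assessment times as "6 monthly post op for the first 2 years and 12-monthly follow-up for next 3 years", a schedule that runs to 5 years.

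**The concern.** A non-inferiority design asks whether a confidence limit for the treatment effect excludes a margin fixed in advance. A log-rank test, when nothing more is said about it, tests equal hazards and has no margin in it. The article states both the margin and the test, and nothing in it brings them together.

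Two things are at stake. First, if the test is run as named and is not significant, the trial has no stated route to a conclusion about non-inferiority, because failing to find a difference does not show that a margin has been excluded. The Discussion cites concern about increased recurrence after TaTME, so the distinction matters. Second, the 80% power belongs to the non-inferiority calculation, and a reader would naturally assume that the named test has it too.

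**Working it through.** **Inputs** (all from The Number of Participants): 3-year DFS 92% TaTME and 95% RLAR; one-sided alpha 20% and power 80%, so z = 0.8416 for each; 165 per arm; 10% loss, leaving 330 × 0.9 = 297 evaluable, or 148.5 per arm. Assumptions of this check: proportional hazards, and no patients lost in the matching.

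**1. Can 330 be reproduced?** No reading that uses all the stated inputs, including the loss, comes within 3% of 330.
- *RLAR tested against TaTME, 90% read as a DFS floor (2 points below 92%), difference scale.* Variance sum = 0.92 × 0.08 + 0.95 × 0.05 = 0.1211. The distance from the true difference (+3 points) to the margin (−2 points) is 0.05. n = (2 × 0.8416)² × 0.1211 / 0.05² = 137.2, so 138 per arm; 138 / 0.9 gives 154 per arm, 308 in total.
- *The same reading on the hazard ratio scale.* Margin HR = ln 0.90 / ln 0.92 = 1.264; true HR = ln 0.95 / ln 0.92 = 0.615. Events = 4 × (2 × 0.8416)² / [ln(1.264 / 0.615)]² = 21.9, so 22; 22 / 0.065 = 339 before loss and 377 after.
- *A log-rank test of 95% against 90%.* 22 events; at an average event rate of 7.5%, 294 patients, or 327 with loss. This is close to 330 but ignores the stated 92%.

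**2. Expected events at 3 years.** Average event rate = (8% + 5%) / 2 = 6.5%. 297 × 0.065 = 19.3 events; with no loss, 330 × 0.065 = 21.5.

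**3. Power of the named test.** HR (TaTME to RLAR) = ln 0.92 / ln 0.95 = 1.626, and ln 1.626 = 0.486. Schoenfeld: power = Φ(√(D/4) × 0.486 − 0.8416).

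| Case | Events D | Power, one-sided 20% |
|---|---|---|
| 3 years, 10% loss | 19.3 | Φ(1.067 − 0.842) = 59% |
| 3 years, no loss | 21.5 | Φ(1.125 − 0.842) = 61% |
| 5 years, 10% loss, constant hazard assumed | 31.4 | Φ(1.362 − 0.842) = 70% |

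The 5-year events are 297 × [(1 − 0.92^(5/3)) + (1 − 0.95^(5/3))] / 2 = 297 × (0.1297 + 0.0819) / 2 = 31.4. Simulated log-rank tests of 3-year data gave 58.9% at 148 per arm and 60.7% at 165 per arm. If matching removed 10% to 30% of the 19.3 events (an assumed range), power would fall to between 57% and 52%.

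**4. Events needed for 80% power.** D = 4 × (0.8416 + 0.8416)² / 0.486² = 48.0. At 6.5% that is 48.0 / 0.065 = 739 evaluable patients, or 739 / 0.9 = 821 recruited.

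**5. Power of a margin-based test with the same patients.** On the difference scale the standard error is √(0.1211 / 148.5) = 0.0286.
- *RLAR against TaTME, floor of 90%:* Φ(0.05 / 0.0286 − 0.842) = 82%. On the hazard ratio scale with 19.3 events: Φ(2.197 × 0.720 − 0.842) = 77%.
- *TaTME against RLAR, 5-point margin (95% to 90%):* the true difference is −3 points, so the distance to the margin is 0.02, and Φ(0.02 / 0.0286 − 0.842) = 44%.

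**The case against.** **The 80% was never claimed for a superiority test.** This is correct. It is stated for the non-inferiority calculation, and on one reading of the margin these patients deliver about that power. A reader might infer from the 48 events that the trial is too small for its purpose. The document does not support that: the 59% is the superiority power of the named test and passes no judgement on the non-inferiority design.

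**A log-rank test can imply non-inferiority.** Also correct. A significant result favouring the tested arm would do so, and the assumed rates point that way if RLAR is the tested arm. It would be too strong to say that the test can never show non-inferiority. The gap concerns the non-significant result, which has a probability of about 41% on the plan's own assumptions (100% − 59%).

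**The 5-year text is a visit schedule.** This stands. A reader might infer that the primary test will run over 5 years, but the outcome is named as 3-year DFS and the data can be censored at 3 years. The 70% is therefore only a sensitivity figure.

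**A doubled hazard would probably be missed.** A reader might infer this from the small event count. At the protocol's own alpha it does not hold: with HR 2 and about 21.9 events, √(21.9 / 4) × ln 2 = 1.62, and the chance of a non-significant result is Φ(0.842 − 1.62) = 22%.

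**No text says that non-significance will be read as equivalence.** True; the objectives speak only of investigating and comparing. The misreading is a risk that the plan leaves open, not a stated intention.

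**The decision rule may be in the unseen analysis plan.** It may. But the article itself fixes both a margin and a primary test that does not use it, so the point is a conflict between two stated elements and not a missing detail.

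**Conclusion.** The point holds as a mismatch between the primary test and the design. The article sizes the trial on a non-inferiority margin, and no analysis it states compares an estimate with that margin. The named log-rank test has about 59% power at one-sided 20% under the stated rates and 10% loss, 61% with no loss, and about 70% if events to 5 years were counted under a constant hazard. None of these reaches 80%. The figures rest on proportional hazards and on matching that loses no one; real matching losses would lower them.

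Whether 330 patients suffice for a proper non-inferiority test cannot be settled from the document, because the margin is undefined: power is about 77% to 82% on one reading and about 44% on another.

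**What to change.** 1. State the margin's scale (DFS difference, DFS floor or hazard ratio), the reference arm and the direction. This comes first, because no decision rule can be written without it.
2. Make the primary analysis the one-sided confidence limit at the stated alpha (an 80% limit for alpha 20%) for the difference in Kaplan-Meier 3-year DFS in the propensity-matched cohort. The hazard ratio with follow-up censored at 3 years is an alternative. Declare non-inferiority only if the limit clears the margin.
3. Keep the log-rank test as secondary, and state that its non-significance is not evidence of equivalence.
4. Restate the power for the margin chosen.

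Alternatively, drop the non-inferiority framing and restate the power as about 59% to 61% for the log-rank test.

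Either route uses the same data and needs changes to the protocol and analysis plan only, best made before any outcome comparison is seen. Defining the margin calls for a clinical justification as well as new wording. The cost is that the restated power may be below 80%, depending on that margin.
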